**Methods/design:**

This multifaceted intervention comprises four nurse-led consultations coupled with four phone calls from a peer support volunteer (GC survivor). The evidence-based intervention will be delivered at critical points in the illness trajectory: pre-treatment, mid-treatment, treatment completion and post-treatment. Nurses and peers undergo 2-day intensive training workshops, are guided by comprehensive study intervention manuals and receive ongoing supervision and support. Eligible patients will have a diagnosis of GC, be scheduled to receive curative radiotherapy, be aged 18 years or over and speak English. Three-hundred and six participants will be randomized to receive usual care or usual care with the intervention package. Study outcome measures will be collected at baseline, day 1 of radiotherapy and 1, 6 and 12 months post radiotherapy. Clinical assessments of vaginal toxicity will occur at baseline, and 3, 6, and 12 months post radiotherapy.

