#### Nurse-led consultations

##### Training

Two specialist cancer nurses will be trained to provide the consultations at each site. The intervention nurse will not be involved in the management of ‘usual care’ patients in order to prevent diffusion of the intervention. Training will comprise online education in distress management, aspects of survivorship and modules on the psychosexual care of women with GC. Training also includes a 2-day workshop facilitated by experts in communication, cancer nursing, patient education and coaching, and psychosexual rehabilitation. The workshop learning objectives are to: (1) gain an understanding of the project including preventing intervention diffusion; (2) develop skills to elicit, explore and respond to patient concerns; and (3) coach and communicate effectively with patients on the use of evidence-based self-care strategies and psychosexual issues. Specific strategies include pelvic floor exercises and the use of vaginal dilators and moisturisers. Training methods included didactic and interactive teaching, rehearsal of skills and constructive feedback using role-plays with actor-patients and the provision of a detailed intervention manual.

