#### Telephone peer support

Each woman will be linked with a peer who will provide four telephone support sessions throughout the treatment course. Peers will be matched to the participant’s medical and personal circumstances such as diagnosis, treatment type, age and area of residence. Approximately 30 peers will be trained over the course of the trial, accounting for peers taking breaks or withdrawing from the study. Each peer will support a maximum of two patients at any one time.

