### Sample size

The treatment effect is conservatively estimated to result in group differences of 0.35 standard deviations for continuous outcome measures
[45-47]. With the Hospital Anxiety and Depression Scale total score (HADS-T) as the primary outcome, to achieve ≥80% power at a 5% significance level, the required sample size in each arm is 130 at the 12-month follow-up. With a patient approach rate estimated at 85%, consent rate estimated at 60% and attrition estimated at 15%, 600 participants will need to be approached to achieve a sample of 260.

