#### Outcome analysis

Outcome analyses will be carried out by fitting linear mixed models (LMM) to each outcome separately. In this case, a sequence of two-level models including random intercepts and slopes will be constructed for each outcome following recommended procedures
[70]. Fully parameterised models will also include fixed effects for time (linear and higher-order polynomials, as appropriate), group, site plus all two-way and cross-level interactions. LMM use all available data, which supports an intention-to-treat approach, and adjusts variance estimates for the correlation between repeated measurements on the same participants. Potential confounders (that is, patient characteristics such as age) will be included as co-variates. These will be centred to facilitate accurate interpretation of results and will be retained in the final models if they explain significant variation in outcomes and improve the precision of the estimates of the treatment effect.

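### The planned model and sample size treat intervention-arm women as independent although they share about 12 nurses and 30 peers; any within-provider correlation makes the standard error too small

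*Protocol article*

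**What the plan says.** **Analysis.** The Outcome analysis section fixes two levels, occasions within women, with random intercepts and slopes. Time, group, site and their interactions are fixed effects. The only correlation it names is within a woman: the approach "adjusts variance estimates for the correlation between repeated measurements on the same participants".

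**Delivery.** Under Nurse-led consultations, Training: "Two specialist cancer nurses will be trained to provide the consultations at each site". Design and setting gives six sites, so 12 nurses. The Training text also keeps the intervention nurse away from usual-care patients. Under Telephone peer support: "Approximately 30 peers will be trained over the course of the trial", and each intervention woman is linked to one peer for four calls.

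**Sample size.** The section assumes "group differences of 0.35 standard deviations for continuous outcome measures" and, "to achieve ≥80% power at a 5% significance level", states that "the required sample size in each arm is 130 at the 12-month follow-up". The only inflation is for approach, consent and attrition. The Abstract gives 306 women to be randomised.

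**The concern.** The intervention is tailored and depends on the skill of the person delivering it. The protocol itself treats that skill as variable. Study integrity provides for review of the first five sessions of every nurse and peer, with feedback, and for adherence checks on 15% of sessions. Women who share a nurse or a peer may therefore have correlated outcomes. This happens in one arm only, which is a partially nested design.

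The planned model counts 130 women as 130 independent pieces of information about the programme. If providers differ, part of the arm difference is the average of 12 particular nurses and about 30 particular peers, and the sampling error of that average is missing from the standard error. The Abstract and Discussion look ahead to wide dissemination, to nurses and peers outside the trial. A few strong providers could then pass for an effect of the programme.

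**Working it through.** **1. The plan's own figure.** Inputs from Sample size: d = 0.35, power 80%, alpha 5% (two-sided; one-sided gives 101 per arm and does not match).
- Normal approximation: n = 2(1.96 + 0.842)²/0.35² = 128.1, so 129 per arm. The exact t calculation gives 130, with power 80.3%.
- At 130 per arm: SE = √(2/130) = 0.1240, and power = Φ(0.35/0.1240 − 1.96) = 80.6%.
- Recruitment: 600 × 0.85 × 0.60 = 306, and 306 × 0.85 = 260.

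The figure reproduces for independent women, with nothing left for a design effect.

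**2. Cluster sizes.** Nurses: 6 × 2 = 12, so 130/12 = 10.83 analysed women each. Peers: 130/30 = 4.33 each.

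**3. Formulas.** For ICCs ρn (nurse) and ρp (peer), with equal clusters:
- DE = 1 + 9.83ρn + 3.33ρp, in the intervention arm only
- variance of the difference = (DE + 1)/130
- SE ratio, true to modelled = √((DE + 1)/2)
- power = Φ(0.35/SE − 1.96)
- type I error of the planned test = 2[1 − Φ(1.96/SE ratio)]

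**4. Results.** The ICCs are assumptions; the documents give none.

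| ρn | ρp | DE | SE ratio | Type I error | Power |
|---|---|---|---|---|---|
| 0 | 0 | 1.00 | 1.00 | 5.0% | 80.6% |
| 0.01 | 0.01 | 1.13 | 1.03 | 5.8% | 78.0% |
| 0.02 | 0.02 | 1.26 | 1.06 | 6.5% | 75.6% |
| 0.05 | 0.05 | 1.66 | 1.15 | 8.9% | 68.7% |
| 0.01 | 0 | 1.10 | 1.02 | 5.6% | 78.7% |
| 0.05 | 0 | 1.49 | 1.12 | 7.9% | 71.5% |
| 0 | 0.01 | 1.03 | 1.01 | 5.2% | 79.9% |
| 0 | 0.05 | 1.17 | 1.04 | 6.0% | 77.4% |

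Nurses drive the result. On this calculation a nurse ICC of about 0.003 is enough to take power below 80%.

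**5. Do the site terms help?** A simulation used 130 women per arm, six sites of assumed unequal size as fixed effects, 12 nurses and 30 peers. It gave type I error of 5.0% with no clustering, and 6.6% / 6.9% / 10.1% at ICCs of 0.01 / 0.02 / 0.05 at both levels. It had site main effects only. The planned site-by-group terms can pick up differences in delivery between sites, but as fixed effects they condition on the nurses who happened to be there. They also do not separate the two nurses within a site. So they add no provider variance to the standard error of the treatment effect.

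**6. Power at the primary time-points.** The primary hypothesis concerns the visit just before radiotherapy and the visit 4 weeks after it, whereas 130 is the 12-month number. With no attrition, 306/2 = 153 per arm would contribute. Cluster sizes become 12.75 and 5.1, and power is 86.5% unclustered, then 83.8% / 81.2% / 73.6% at 0.01 / 0.02 / 0.05. The larger clusters raise the type I error slightly, to 5.9% / 6.9% / 9.7%.

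**7. Power with baseline adjustment.** Assume a baseline correlation of 0.5 and 130 per arm. If adjustment multiplies all variance by 1 − 0.25 = 0.75, power is 90% unclustered and 81% with both ICCs at 0.05. If it shrinks only the between-woman variance, the variance at ICCs of 0.05 is (0.90 × 0.75 + 0.75)/130 + 0.05/12 + 0.05/30 = 0.0168. That gives power of about 77%, or about 81% with 153 per arm.

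**The case against.** **The size is assumed, and may be small.** True. At ICCs of 0.01 the standard error grows by 3% and power falls by under three points. Manuals, two-day workshops and session review should hold provider variation down, and the peer contribution is minor. What stands is the direction: any positive correlation makes the planned standard error too small, and the sample size leaves no margin.

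**The trial may still have 80% power.** Also true. A reader might infer that real power is 69% to 78%. The documents do not support that. Those figures belong to a two-group comparison at 12 months, whereas the planned model uses repeated measures including baseline, and up to 153 per arm may contribute at the primary time-points. Steps 6 and 7 show that power near 80% is possible even at ICCs of 0.05. Neither gain repairs the standard error or the type I error.

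**Site-by-group terms are planned.** They are, and they do model differences in delivery between sites. For the reasons in step 5 they do not carry provider variance into the inference.

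**This belongs in the analysis plan.** A condensed article may leave detail to a plan that is not shown, and the Statistical analyses section lets methods be revised once the data have been inspected. But the article does state the model levels, the correlation handled and the sample size, and these do not fit the delivery structure it also states. The revision clause does not mention clustering, and a variance structure should be fixed before the data are seen.

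**Simple nesting may not hold.** The article does not say that one nurse sees a woman throughout. Peers are matched on diagnosis, treatment type, age and area, so a peer effect would partly reflect patient characteristics. With about four women per peer it may also be poorly estimated. This stands, and it shapes the fix.

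**Conclusion.** The point holds in conditional form. The stated model and sample size ignore provider clustering that exists in one arm only. If outcomes correlate within provider, mainly within nurse, the interval for the treatment effect is too narrow and the test exceeds its 5% level: by about 1 to 4 percentage points for ICCs of 0.01 to 0.05 at both levels, with equal cluster sizes. Design and setting expects unequal recruitment by site, which would make these figures somewhat optimistic.

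A reader might go further and conclude that the standard errors are certainly wrong by a known amount. With no ICC in the documents, that cannot be shown. What can be said about power is narrower: the stated 80% assumes no provider clustering, and the plan's own calculation falls below 80% at a very small nurse ICC.

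**What to change.** 1. Record nurse and peer identifiers for every intervention woman.
2. Prespecify a partially nested model: a random nurse effect in the intervention arm only, with small-sample (Satterthwaite) degrees of freedom. If the fixed site-by-group terms stay, the nurse variance rests on 12 − 6 = 6 degrees of freedom, so this matters.
3. Add a random peer effect in that arm if it can be estimated; otherwise report it as a sensitivity analysis.
4. Assign a woman seen by more than one nurse to the nurse of session 1, or use a multiple-membership term. State which.
5. State in Sample size that the 80% assumes no provider clustering, and show power over an explicit ICC range for the model actually planned, at the primary time-points.

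No extra patients are needed. Eligibility and consent procedures give the data manager the task of coordinating nurses and peers, so the identifiers are probably at hand, though the article does not say so. The cost is slightly wider intervals, a less favourable stated power, and some risk that the peer term cannot be fitted.

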### Study integrity

The study design and reporting will adhere to the Consolidated Standards of Reporting Trials (CONSORT) statement
[48]. Usual care practice will be monitored yearly with a questionnaire administered to nurses most involved with the usual care of women with GC receiving radiotherapy at each site. A consecutive sample will be randomly allocated at the central site by computer with a weighted-biased coin method 1:1 to either intervention or usual care arms. Participants will be stratified according to treating hospital and treatment type. Minimisation will be used to balance the randomisation across the strata.

Participants will not be informed of their allocation until the baseline questionnaire has been received. Blinding of patients and providers to experimental arm cannot be achieved with this study design, however outcome assessment will be by self-reported questionnaire, thereby obviating the need for researcher blinding. Usual care arm participants will receive a booklet on their specific cancer diagnosis, treatment, and psychosexual recovery to meet minimal ethical standards
[49], and information will be provided as per usual practice by their treatment team. Reasons for attrition will be recorded and recruitment and dropout bias assessed.

All nurse and peer sessions will be audio-taped and a random sample of 15% of sessions will be assessed for adherence to protocol. Length of sessions will be reported. The first five calls or consultations made by each peer and nurse will be reviewed and feedback provided on adherence to protocol, use of communication and coaching skills and areas for improvement.

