#### Demographics and clinical variables

Demographic details will be recorded by the patient on the baseline questionnaire and include age, postcode, marital and education status, employment situation and occupation, living arrangements, whether they have children, sexual orientation, country of birth and first language, menopausal status, and antidepressant or sedative use. Clinical details of diagnosis, diagnosis date, disease stage, Eastern Cooperative Oncology Group (ECOG) performance status, histopathology grade, history of another cancer, treatment for a past diagnosis, current treatment type (external beam, brachytherapy, concurrent chemotherapy), prior treatments (surgery, chemotherapy), involvement with hospital services and Charlson co-morbidity index will be completed by the data manager on a case record form.

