### Statistical analyses

All data will be analyzed through SPSS Windows Version 20.0 (SPSS, Chicago, IL, USA). After inspection of the data, the appropriateness of all methods described below will be reviewed and revised if necessary.

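### Treatment type balances the allocation but has no assured place in the outcome model, and the retention and revision clauses leave the primary model open until the data are seen

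*Protocol article*

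**What the plan says.** **Allocation (Study integrity).** Women are "randomly allocated at the central site by computer with a weighted-biased coin method 1:1". The section adds: "Participants will be stratified according to treating hospital and treatment type", and then "Minimisation will be used to balance the randomisation across the strata". Hospital and treatment type are thus both design factors.

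**Model (Outcome analysis).** The full linear mixed model has "fixed effects for time (linear and higher-order polynomials, as appropriate), group, site plus all two-way and cross-level interactions". Site is there; treatment type is not. Of other variables the section says: "Potential confounders (that is, patient characteristics such as age) will be included as co-variates". These are then "retained in the final models if they explain significant variation in outcomes and improve the precision of the estimates of the treatment effect".

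**Revision (Statistical analyses).** "After inspection of the data, the appropriateness of all methods described below will be reviewed and revised if necessary". No concealment of arm and no cut-off date is attached to this.

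**Availability.** Demographics and clinical variables lists current treatment type among the items that the data manager completes on the case record form, so adjustment is feasible.

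**The concern.** A factor that the allocation is forced to balance makes the arms more alike than simple randomisation would. If that factor predicts the outcome and the model ignores it, the model's standard error is larger than the true one: the test becomes conservative and power is lost. The article follows the usual principle for one minimisation factor and not for the other. If treatment type does enter, it must first pass a test on the outcome data, so the presence of a design factor in the final model depends on the result.

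The wider issue is that three choices are left to the data: the order of the time polynomials, the covariates kept, and, through the revision clause, any method at all. Patients and providers know the arm and the primary outcome is self-reported. A reader could not tell a planned primary result from one chosen afterwards.

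**Working it through.** **1. The plan's own figure.** Inputs from Sample size: difference 0.35 SD, 5% significance, at least 80% power, 130 per arm. With a two-sided test the normal approximation gives 129 per arm, and the t test gives 80.3% power at 130. (A one-sided test would need only 101, so the plan's figure is two-sided.) The figure reproduces and is not in dispute.

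**2. Effect of omitting a balanced factor, one time-point.** Let R² be the share of HADS-T variance that treatment type explains. The article does not give it, so a range is assumed. With total SD 1 and 130 per arm:

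- model SE when omitted = √(2/130) = 0.124; true SE = 0.124 × √(1−R²)
- type I error = 2 × [1 − Φ(1.96/√(1−R²))]
- non-centrality = 0.35 × √65 = 2.82
- power, omitted = Φ((2.82 − 1.96)/√(1−R²))
- power, adjusted = Φ(2.82/√(1−R²) − 1.96)

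| Assumed R² | Model SE ÷ true SE | Type I error, omitted | Power, omitted | Power, adjusted | Difference (points) |
|---|---|---|---|---|---|
| 0.02 | 1.010 | 4.8% | 80.8% | 81.3% | 0.5 |
| 0.05 | 1.026 | 4.4% | 81.2% | 82.5% | 1.3 |
| 0.10 | 1.054 | 3.9% | 81.8% | 84.5% | 2.7 |
| 0.20 | 1.118 | 2.8% | 83.2% | 88.4% | 5.2 |

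**3. Check by simulation.** Biased-coin minimisation was simulated on six sites and three treatment types, with 260 women, 3,000 runs per setting and site always in the model. The coin weight of 0.8, the site shares and the treatment-type shares are assumptions. At R² = 0.10, type I error was 0.039 with treatment type omitted and 0.051 with it included; power was 81.2% and 83.9%. Monte Carlo error on the type I figures is about 0.004. This agrees with the table.

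**4. The retention rule applied to treatment type.** In the same simulation, treatment type was significant in about 51% of trials at R² = 0.02, 91% at 0.05 and nearly 100% at 0.10. Type I error after selection was 0.049 to 0.052 over R² = 0.02 to 0.20. At R² = 0 it was 0.056, but the two fixed models gave 0.056 and 0.055 there, so that is not an effect of selection. This tests one candidate covariate only, not an open list and not the revision clause.

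**5. Group-by-time contrast.** The primary endpoint is worded as distress from baseline to follow-up. If treatment type shifts a woman's HADS-T by the same amount at every visit, the shift drops out of her change over time, and the random intercept absorbs it in the mixed model. A small simulation (260 women, three time-points, random intercept and slope, assumed variances, only 15 runs per setting) gave a ratio of 1.000 between the group-by-time standard errors without and with a treatment-type main effect, at R² of 5% and of 10%. A loss arises only if treatment type predicts change over time.

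**The case against.** The strongest reply is that the article does not exclude treatment type; it only fails to list it. The class of patient characteristics is open, treatment type is recorded, and a condensed article normally leaves the full covariate list to the analysis plan. If treatment type is a candidate, the rule would nearly always keep it at the very R² values where omission costs something. Part of this stands: the losses in the table describe outright omission, which the text does not make certain. But the article is not silent. It sets out a full model that names one design factor and not the other, and it states the rule that any further covariate must pass.

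Two stronger readings are tempting and are not supported:

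- A reader might infer that leaving out treatment type inflates false positives. The error goes the other way, and power stays above the planned 80% at every R² in the table.
- A reader might infer that the retention rule makes the 95% interval invalid. The rule screens on prognostic value and precision, not on the size of the treatment estimate, and simulated type I error stayed near 5%.

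The revision clause can also be read as an ordinary check that the methods suit the data. That may be its intent, but its wording covers all methods and sets no condition on when, or with what knowledge of arm, they may change.

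**Conclusion.** The point holds, at minor to moderate weight. A minimisation factor has no assured place in the outcome model, and the retention rule and revision clause together allow the primary model to be settled after the data are seen.

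The measurable cost of omission is small and conservative. It rests on an assumed R², on 130 per arm and on a comparison at a single time-point; at an R² of 0.05 the excess in the standard error is 2.6%, and below that it is less. For a contrast in change over time the cost is near zero unless treatment type affects the course of distress. The effect of choosing the model after inspection cannot be sized from the article. It is the more serious part because it bears on whether the primary result can be read as pre-specified.

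**What to change.** 1. Include treating hospital and treatment type, the latter coded as at allocation, with their time terms, in every outcome model regardless of significance.
2. Replace the retention rule with a short list of covariates named in advance. Use any others only in sensitivity analyses.
3. State how baseline HADS-T is handled: as a response time-point or as a covariate, not both. Table 1 and the baseline-to-follow-up wording of the primary endpoint suggest that it is now a response.
4. Limit the revision clause to assumption checks made blind to arm, and report any later change as post hoc.

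All the variables are already collected and the sample size stays at 130 per arm. The cost is a change of wording, one decision on baseline, and a few degrees of freedom out of about 260 women.
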